## Abstract

**Background:**

Following sentinel lymph node biopsy (SLNB), the axillary recurrence rate is very low although SLNB has a false-negative rate of 5–10%. In the ACOSOG Z0011 trial, non-sentinel positive-lymph nodes were found in more than 20% of the axillary dissection group; the SLNB only group did not have a higher axillary recurrence rate. These findings raised questions about the direct therapeutic effect of the SLNB. SLNB has post-surgical complications including lymphedema. Considering advances in imaging modalities and adjuvant therapies, the role of SLNB in early breast cancer needs to be re-evaluated.

**Methods:**

The NAUTILUS trial is a prospective multicenter randomized controlled trial involving clinical stage T1–2 and N0 breast cancer patients receiving breast-conserving surgery. Axillary ultrasound is mandatory before surgery with predefined imaging criteria for inclusion. Ultrasound-guided core needle biopsy or needle aspiration of a suspicious node is allowed. Patients will be randomized (1:1) into the no-SLNB (test) and SLNB (control) groups. A total of 1734 patients are needed, considering a 5% non-inferiority margin, 5% significance level, 80% statistical power, and 10% dropout rate. All patients in the two groups will receive ipsilateral whole-breast radiation according to a predefined protocol. The primary endpoint of this trial is the 5-year invasive disease-free survival. The secondary endpoints are overall survival, distant metastasis-free survival, axillary recurrence rate, and quality of life of the patients.

**Discussion:**

This trial will provide important evidence on the oncological safety of the omission of SLNB for early breast cancer patients undergoing breast-conserving surgery and receiving whole-breast radiation, especially when the axillary lymph node is not suspicious during preoperative axillary ultrasound.

**Trial registration:**

ClinicalTrials.gov, NCT04303715. Registered on March 11, 2020.

## Background

Axillary surgery has been an essential breast cancer surgery since the introduction of Halsted radical mastectomy of the late nineteenth century. However, the survival benefit of axillary surgery has not been proven in a randomized controlled trial. In the National Surgical Adjuvant Breast and Bowel Project (NSABP) B-04 trial for clinically lymph node-negative breast cancer patients, overall survival (OS) was not different after radical mastectomy and total mastectomy without axilla surgery although approximately 40% of the radical mastectomy group were lymph node-positive [1].

Sentinel lymph node biopsy (SLNB) has replaced axillary lymph node dissection (ALND) for most cases of operable early breast cancer since it was introduced in 1994 to reduce the complication of ALND. In the NSABP B-32 study, the 8-year disease-free survival (DFS) did not differ in the ALND group and SLNB with ALND only group if the SLNs were positive (*p* = 0.54). The false-negative rate (FNR) for SLNB was 9.8% [2]. However, SLNB alone had significant complications. In the B-32 trial, the incidence of lymphedema was 7.5%, and the prevalence of sensory and other limitations of movement was 5–8%. Some studies have reported that SLNB only is associated with a reduced global health status QoL score [3].

The most important goal is to determine whether SLNB has a therapeutic role. SLNB is not a perfect procedure for removing metastatic lymph nodes. In the pivotal NSABP B-32 trial, the FNR of SLNB was 9.8% [2]. The FNR of the SLNB procedure was generally reported to be between 4.6 and 16.7% [4]. However, the axillary recurrence rates after SLNB only was between 0 and 1.5%, which is much lower considering the FNR of the SLNB procedure [5]. Furthermore, in the ACOSOG Z0011 study, 23.7% of the control group (axillary node dissection) patients had additional metastatic lymph nodes other than sentinel nodes. However, the axillary recurrence rate or DFS did not differ in the SLNB only and control groups [6]. These findings raise questions about the need to remove sentinel lymph nodes, especially in patients who undergo breast-conserving surgery and whole-breast radiation.

The axillary lymph node status became less important for deciding on adjuvant therapies for early breast cancer. In human epidermal growth factor receptor 2 (HER2)-positive or triple-negative breast cancers, adjuvant chemotherapy and/or HER2 targeted therapy was indicated regardless of lymph node status. For estrogen-receptor-positive HER2-negative breast cancers, multigene assays, such as the 21-gene or 70-gene assay, are used to guide adjuvant chemotherapy decisions.

With advances in imaging techniques, the accuracy of presurgical lymph node status prediction based on axillary ultrasonography (AUS) with or without core biopsy or fine-needle aspiration (FNA) has increased significantly. In a study by Cho et al., sonographic classification of axillary lymph nodes showed 85% sensitivity and 78% specificity for predicting metastasis when a cutoff for cortical thickness of 2.5 mm was used [7]. In the SOUND trial, preoperative AUS resulted in 15.5% of FNR, which was reduced to 8.1%, excluding isolated tumor cells and micrometastases, and 4.9%, considering only metastases of > 3 mm, which are the only lesions that AUS can reliably detect. The NPV was 95% after excluding isolated tumor cells and micrometastases [8].

Taking everything into consideration, this clinical trial aims to show whether SLNB can be omitted in a specific patient group. If there is no significant difference between the SLNB and non-SLNB groups, patients would have increased quality of life by eliminating unnecessary surgical procedures.

## Methods and design

### Study design

The NAUTILUS trial is a prospective multicenter randomized controlled trial. Ten tertiary care hospitals in South Korea are participating in this trial. Patients with invasive breast cancer who have tumors less than 5 cm and clinically negative axillary lymph nodes and are expected to undergo breast-conserving surgery (BCS) are randomized (1:1) to the SLNB and no-SLNB groups. Eligible patients undergo AUS for the assessment of lymph node status before enrollment. Core-needle biopsy or fine-needle aspiration of the node is performed if a patient has a suspicious lymph node based on AUS findings (Fig. 1). The patients are blinded to the randomization process until the surgery. The study is expected to last for 7 years, with 2 years for registration and 5 years for follow-up (Fig. 2). Patient recruitment was started on September 1, 2020, and the first patient was recruited on September 15, 2020. The enrolment is estimated to be completed in April 2022.

**Fig. 1 Fig1:**
[figure not shown]
NAUTILUS trial: Study design

**Fig. 2 Fig2:**
[figure not shown]
Diagram for the study process

The design and processes of the NAUTILUS study follow the guidelines for clinical trial protocols as specified by the Standard Protocol Items: Recommendations for Interventional Trials (SPIRIT) 2013 statement. This trial is registered at ClinicalTrials.gov (NCT04303715) on March 11, 2020.

### Study participants

Participating patients are included or excluded according to the specified criteria. The inclusion criteria are as follows: 1) 19 years or older with pathologically confirmed invasive breast cancer; 2) no clinical or radiological evidence of distant metastasis; 3) Eastern Cooperative Oncology Group (ECOG) performance status of 0–2; 4) negative axillary lymph node determined clinically and based on AUS; 5) for an eligible patient who has one minimally suspicious axillary lymph node based on AUS findings, confirmation of negative lymph node metastasis with core needle biopsy or FNA is mandatory; 5) BCS candidate with scheduled postoperative whole-breast irradiation; 6) follow-up after treatment is possible without physical, mental, or geographical restriction; 7) and full understanding of the written informed consent.

The exclusion criteria are as follows: 1) history of any cancer within the past 5 years except for well-treated skin cancers other than melanoma, thyroid cancer, and other in situ carcinoma excluding ductal carcinoma in situ of the breast; 2) bilateral breast cancer; 3) pre-treatment with neoadjuvant therapy; 4) pregnant or breast-feeding women; and 5) inability to understand and fill out questionnaires.

### Sample size calculation

We designed the NAUTILUS study to determine whether the no-SLNB group was not inferior to the standard SLNB group. In the NSABP B-32 study, the 5-year DFS was 88.6% for cT1–2 N0 breast cancer [2]. We assumed that the DFS of our study patients would be lower than this because lymph node-positive patients will be included in our study. In the ACOSOG Z0011 study, the 5-year DFS was 83.9% for cT1–2 N1 (1 or 2 lymph node-positive) [6]. We assumed that the DFS of our study patients would be higher than this. As a result, the expected 5-year DFS of the control group of our study is 86%.

The 5% non-inferiority margin, 80% power, 5% two-sided significance level resulted in a sample size of 780 per study arm. Assuming a 10% dropout rate, 1734 patients need to be randomized. Patients are recruited competitively from each institution.

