### Statistics

For nominal variables such as self-reported complications in each arm/group, the total number of patients, percentile, and frequency will be presented and analyzed using the chi-squared test or Fisher’s exact test. Continuous variables, such as age and tumor size, will be summarized using descriptive statistics (mean, standard deviation, median, etc.), followed by analysis using Student’s t-test or the Mann-Whitney U-test as a non-parametric test.

The statistical significance of the 5-year DFS, which is the primary endpoint, overall survival, and distant DFS will be determined using Kaplan-Meier analysis and the log-rank test. Cox proportional hazard regression analysis will be used to assess the prognostic significance of variables. For every statistical analysis, a *p*-value of < 0.05 will be considered statistically significant.

An interim analysis for the primary endpoint is planned once, and an interim analysis is performed 5 years from the date of IRB approval, and a final analysis is performed after at least 224 events have occurred. Disease-independent death is defined as a competing event. Fine and Gray regression is performed to verify the statistical hypothesis for comparison between groups, and the significance level used for interim and final analysis is calculated based on the O’Brien Fleming α-spending function, and the analysis uses SAS 9.4 Proc seq test.

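### The 224-event hazard-based final analysis does not by itself secure the 80% power at two-sided 5% on which the sample size is stated

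*Protocol article*

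**What the plan says.** Sample size calculation (protocol article) assumes a control 5-year DFS of 86% and states: "The 5% non-inferiority margin, 80% power, 5% two-sided significance level resulted in a sample size of 780 per study arm". It then adds: "Assuming a 10% dropout rate, 1734 patients need to be randomized". The margin is given only as 5%, next to a 5-year DFS percentage. No hazard ratio and no number of events appears there.

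Statistics lists Kaplan-Meier analysis and the log-rank test for 5-year DFS. It then treats deaths unrelated to the disease as competing events and names Fine and Gray regression as the method that verifies the hypothesis. One interim analysis is planned, with O'Brien-Fleming alpha spending. On timing it says that "a final analysis is performed after at least 224 events have occurred". The origin of 224 is not given.

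Two statements bear on how many events can accrue. Study design describes a 7-year study, "with 2 years for registration and 5 years for follow-up". Interventions and follow up limits follow-up to at most 5 years after surgery.

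**The concern.** The sample size section counts patients for a margin in percentage points at 5 years. The Statistics section tests with a regression on a hazard-type scale, and the power of such a test depends on the number of events. The two sections share one stated level and one stated power, but the event count that triggers the final analysis looks too small for both to hold.

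This matters because a non-inferiority trial with less power than stated has a larger chance of failing to show non-inferiority when the arms are truly equal. At 71% power that chance is about 29%, against the 20% that the article implies. The margin, level and information target also fix the interim and final boundaries, so they have to agree before the first look.

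**Working it through.** **Inputs.** Control 5-year DFS 86%, margin 5 points (so 81% at the margin), 80% power, two-sided 5% (2.5% in the non-inferiority direction), 780 per arm and 10% dropout, all from Sample size calculation. At least 224 events, from Statistics. 1:1 allocation, from the abstract. Two years of accrual in a 7-year study, from Study design. At most 5 years of follow-up per patient, from Interventions and follow up.

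**Assumptions added here.** Proportional hazards, exponential DFS and truly equal arms. Where loss is included, it is exponential and reaches 10% by 5 years.

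**1. The plan's own 780 per arm.** For a difference in 5-year proportions with equal true rates:

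- n per arm = (1.960 + 0.842)² × 2 × 0.86 × 0.14 / 0.05² = 7.849 × 0.2408 / 0.0025 = 756.0, or 757 rounded up.
- Power at 780: standard error = √(0.2408/780) = 0.01757; Φ(0.05/0.01757 − 1.960) = 81.2%.
- Dropout: 780/0.9 = 866.7, so 867 per arm and 1,734 in total.

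So 780 and 1,734 agree with the stated level and power on the absolute scale.

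**2. The same margin on the hazard scale.** HR margin = ln 0.81 / ln 0.86 = 1.397, and ln 1.397 = 0.3344.

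Events for 80% power:

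- Schoenfeld: 4(z_α + 0.842)² / 0.3344²
- Freedman: (z_α + 0.842)² × [(1.397 + 1)/(1.397 − 1)]²

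| Level | Schoenfeld | Freedman |
|---|---|---|
| two-sided 5% (z = 1.960) | 281 | 286 |
| one-sided 5% (z = 1.645) | 222 | 226 |

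**3. Power at 224 events.** √(224/4) × 0.3344 = 2.503.

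- Two-sided 5%: Φ(2.503 − 1.960) = 70.6% (Freedman form: 69.8%).
- One-sided 5%: Φ(2.503 − 1.645) = 80.4% (Freedman form: 79.8%).
- Two-sided 5% with one O'Brien-Fleming look at 40 to 80% of the information: 69.7 to 70.6%.

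**4. Events that 1,734 patients can supply.** Event hazard = −ln 0.86 / 5 = 0.03016 per year; loss hazard = −ln 0.90 / 5 = 0.02107 per year.

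| Follow-up | Loss | Events | Power, two-sided 5% |
|---|---|---|---|
| 5 years per patient | none | 1,734 × 0.140 = 243 | 74% |
| 5 years per patient | 10% by 5 years | 1,734 × 0.133 = 231 | 72% |
| to year 7, 2-year accrual | none | 1,734 × 0.165 = 287 | 81% |
| to year 7, 2-year accrual | 10% by 5 years | 1,734 × 0.156 = 270 | 78% |

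Only the third row reaches 80%.

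**The case against.** **The sample size sentence is not wrong.** This stands. Step 1 reproduces it on the absolute scale. The fault lies between the two sections and belongs with the event trigger in Statistics.

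**224 is a minimum.** This stands in part. The flat 71% applies only if the analysis is made at the floor. More events may accrue, but under the 5-year cap they bring power only to 72 to 74%. Reaching 80% needs follow-up to year 7 with almost no loss, and the trigger does not require that.

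**The hazard-ratio margin is not the sponsor's.** This stands as a limit. The article gives no hazard ratio, and the full protocol or analysis plan may define one. The conversion needs proportional hazards, but some such margin is implied once a hazard-type regression tests the hypothesis.

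**Kaplan-Meier analysis is also listed.** True, and it could support an absolute comparison. The article nevertheless names Fine and Gray regression as the method that verifies the hypothesis.

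**A stronger reading.** Because 224 lies between the two one-sided 5% counts (222 and 226), a reader might infer that the trial was sized at one-sided 5% and will run at twice the expected false non-inferiority rate. The document does not support that. It nowhere states a one-sided 5% level and does not derive 224. The figure is also close to the 218 events expected from 1,560 patients at 14% (1,560 × 0.14 = 218.4), so it may be a timing figure.

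**Conclusion.** The sample size and the final analysis do not fit together. The 780 per arm supports the stated 80% power for an absolute 5-year difference at two-sided 5%. For the event-driven hazard-type test that the article describes, the stated power is not secured. It is about 71% at the 224-event floor, 72 to 74% with 5 years of follow-up per patient, and 78 to 81% only with follow-up to year 7. About 281 to 286 events would be needed for 80%.

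These figures rest on the 1.397 hazard-ratio margin, proportional hazards, exponential DFS at 86% in both arms, and the loss pattern shown. If the 14% event rate includes deaths that Statistics counts as competing, the events of interest would be fewer and power lower. Whether one-sided 5% was intended cannot be settled from the document.

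**What to change.** In Statistics, state the non-inferiority margin on the scale of the primary test, and make the level and power in Sample size calculation agree with it. There are two ways:

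- **(a) Keep the hazard-based test.** State the margin (about 1.40 if the 5-point margin is converted). Restate power at two-sided 5% as about 71% at 224 events, or 72 to 74% with 5 years of follow-up per patient. If one-sided 5% was intended, correct the word two-sided in Sample size calculation instead. Raising the trigger to 281 to 286 events would restore 80%, but step 4 shows this is reachable only with follow-up to year 7 and almost no loss.
- **(b) Test the absolute 5-year DFS difference against −5 points at one-sided 2.5%.** This matches the 780 per arm and keeps about 80% power with the planned 1,734. The handling of competing deaths must then be reconciled with the DFS estimate being tested.

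State how 224 was obtained, and settle the choice before the interim analysis.

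Neither the restatement under (a) nor option (b) needs more patients. The cost of (a) is a less favourable stated power or an openly one-sided 5% level. The cost of (b) is a change of primary test in a trial that has already started recruiting, which needs a documented amendment.

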### Screening and randomization

Participants undergo screening tests that will assess eligibility according to the inclusion/exclusion criteria. All procedures are performed after obtaining informed consent from the patients. Screening includes history taking, physical examination, pregnancy test, breast ultrasonography, and mammography. Additional tests can be performed if deemed necessary. AUS is performed by radiologists at each center to evaluate axillary lymph nodes. Written informed consent is obtained from each participant before enrollment by investigators. After enrollment, the randomization is conducted using a web-based system by investigators. Details of the randomization procedure will not be shared with the investigators of the clinical trial sites. The randomization table is prepared using SAS Version 9.4 (SAS Institute Inc., Cary, USA) with a stratified block randomization method. The stratification factors are treatment center and tumor size. The Medical Research Collaborating Center of Seoul National University Hospital (MRCC) created a random assignment table and operate it through web random assignment. Patients are blinded to their designated treatment arm before surgery to prevent bias or early dropout. During the randomization procedure, the investigator should provide the following information for each subject (protocol number, name of the clinical trial institution, screening number, tumor size). A randomization number is assigned through the web site, and a written confirmation of the subject is printed out and stored in the clinical trial basic document file provided to the institution. The randomization number applies to all case records and all subsequent correspondence related to the subject. Only pre-authorized investigators can access this randomization system.

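### Randomisation is stratified by center and tumor size, but the named primary comparison does not use these factors; using them is a free, small gain in precision

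*Protocol article*

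**What the plan says.** Under Screening and randomization, the article describes a table prepared "with a stratified block randomization method" and adds: "The stratification factors are treatment center and tumor size". The investigator enters the institution and the tumor size when a patient is randomised. Study design gives the number of centers: "Ten tertiary care hospitals in South Korea are participating in this trial". Allocation is 1:1.

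The Statistics section names the primary comparison twice. First, significance of the 5-year DFS, "which is the primary endpoint, overall survival, and distant DFS will be determined using Kaplan-Meier analysis and the log-rank test". Later: "Fine and Gray regression is performed to verify the statistical hypothesis for comparison between groups". Neither sentence mentions strata or covariates. Cox regression appears only for the prognostic value of variables, not for comparing the arms.

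The Sample size calculation section sets the margin on the absolute scale: "The 5% non-inferiority margin, 80% power, 5% two-sided significance level resulted in a sample size of 780 per study arm". The assumed control 5-year DFS is 86%. The article states no hazard ratio margin.

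**The concern.** Stratified blocks force the arms to be nearly equal within each center and tumor-size group, so differences between groups in prognosis hardly contribute to the real sampling variation of the treatment comparison. A standard error that ignores the groups still counts that variation and comes out too large. The interval is then wider than it needs to be, and non-inferiority is a little harder to show when it is true.

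Both factors can plausibly affect outcome here. The sponsor chose them for stratification, and the Interventions and follow up section leaves adjuvant systemic therapy, the tumor-bed boost, further axillary surgery in the control arm and the visit interval to each center. At stake is a little power, not the validity of the result.

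**Working it through.** **Inputs from the article.** 10 centers; 1:1 stratified blocks; control 5-year DFS 0.86; margin 0.05; 780 per arm and 1,734 randomised; 2 years of accrual and 5 of follow-up; 10% dropout; final analysis at 224 events or more.

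**Assumed, because the article gives no figures.** Two tumor-size groups with 35% larger tumors; block size 4; low / middle / extreme prognostic strength, meaning a tumor-size hazard ratio of 2 / 2 / 3 and a between-center SD of the log hazard of 0.2 / 0.4 / 0.6.

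**Step 1: the plan's own figure.** n per arm = (1.960 + 0.842)² × 2 × 0.86 × 0.14 / 0.05² = 757 after rounding up, against 780 stated (3% apart). Then 780 / 0.9 = 867 per arm, and 2 × 867 = 1,734, as stated. Stratification enters neither figure.

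**Step 2: approximate size of the excess standard error.** The total variance of a 5-year DFS indicator is 0.86 × 0.14 = 0.1204. The between-stratum part is roughly (S ln S)² × Var(log hazard). Here S ln S = 0.86 × ln 0.86 = −0.1297, whose square is 0.0168. Var(log hazard) is (ln HR)² × 0.35 × 0.65 + SD². With f the between-stratum share, the standard error is inflated by 1/√(1 − f) − 1.

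| Assumption | Var(log hazard) | Between-stratum variance | f | SE too large by |
|---|---|---|---|---|
| Low | 0.1093 + 0.04 = 0.149 | 0.0025 | 2.1% | 1.1% |
| Middle | 0.1093 + 0.16 = 0.269 | 0.0045 | 3.8% | 1.9% |
| Extreme | 0.2746 + 0.36 = 0.635 | 0.0107 | 8.9% | 4.8% |

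**Step 3: simulation.** 4,000 trials per scenario, N = 1,734, 20 strata, no competing deaths; Cox regression stands in for log-rank and for Fine and Gray. The Monte Carlo error of a 2.5% rate is √(0.025 × 0.975 / 4,000) = 0.25 points; that of an empirical SD is about 1/√8,000 = 1.1%.

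| | Low | Middle | Extreme |
|---|---|---|---|
| Unstratified Kaplan-Meier difference, equal arms: empirical SD / model SE | 0.0170 / 0.0171 | 0.0170 / 0.0171 | 0.0165 / 0.0171 |
| Same, true difference 5 points | 0.0182 / 0.0183 | 0.0178 / 0.0183 | 0.0174 / 0.0183 |
| False non-inferiority at a true 5-point difference: Kaplan-Meier | 2.7% | 2.2% | 2.2% |
| Same: unstratified Cox | 2.5% | 2.1% | 2.4% |
| Power at hazard ratio 1: unstratified / stratified Cox | 79% / 79% | 79% / 78% | 79% / 78% |

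With equal arms the Kaplan-Meier standard error is 0.6% to 3.6% too large. At the margin it is 0.5% to 5.2% too large, the top value belonging to the extreme case.

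**Step 4: what this costs in power.** Power = Φ((0.05 − 1.96 × SE) / SD).
- Low: Φ(0.0165 / 0.0170) = 83.4%. With the SE equal to the SD it is Φ(0.0167 / 0.0170) = 83.7%.
- Extreme: Φ(0.0165 / 0.0165) = 84.1%. With the SE equal to the SD it is Φ(0.0177 / 0.0165) = 85.8%.

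The loss is therefore 0.3 to 1.7 points. Simulating the combined within-stratum estimator directly gives gains of about 0.4 to 1.3 points when combining over tumor size only. Combining over size by center gains 1 to 1.5 points under low to middle assumptions. Its false non-inferiority rate is 2.2% to 2.8%. Stratified Cox gains nothing.

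**Step 5: the hazard ratio scale.** A 5-point loss corresponds to a hazard ratio of ln 0.81 / ln 0.86 = 1.397. If that is the true ratio within every stratum, the unstratified estimate averages 1.392 / 1.386 / 1.363, against 1.400 / 1.399 / 1.397 stratified. Judged against a within-stratum margin of 1.397, false non-inferiority is 2.6% / 2.8% / 3.5% unstratified and 2.3% / 2.6% / 2.7% stratified. Only the extreme case stands clear of simulation error.

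**Step 6: sparseness.** 224 events over 10 × 2 = 20 strata is about 11 events per stratum.

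**The case against.** The strongest reply is that the article never says the tests are unstratified. It is silent, it condenses a longer protocol, and an analysis plan not shown here may name the strata. That stands, and this point is no claim of an omission. It is a suggestion on the tests as named, in a section detailed enough to give the competing event, the event count, the spending function and the software procedure.

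A second reply is that nothing is gained. That is right for stratified Cox. It is not right for the 5-year Kaplan-Meier difference, where the gain is small but real under the assumed strengths.

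A third is that the prognostic strengths are invented and competing deaths are left out. The sizes do depend on these choices. The direction of the standard error does not, provided the factors are prognostic.

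A reader might infer something stronger: that leaving out the strata pulls the hazard ratio towards 1 and so favours non-inferiority. The document does not support this. Its margin is a difference in overall 5-year DFS, which is the quantity an unstratified comparison estimates, and the simulated error at that margin is close to 2.5%. The attenuation would matter only against a within-stratum hazard ratio margin, and none is stated. Even then the oversized standard error offsets part of it.

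**Conclusion.** The point holds as a free improvement with a small effect. The primary comparison as named leaves out the factors used to randomise. Taking the 5-year Kaplan-Meier difference as the analysis that addresses the 5-point margin, its standard error is about 1% to 4% too large and about 1 point of power is lost; the most extreme assumptions push the excess to about 5%. The analysis remains valid, and the error is conservative. These sizes rest on assumed tumor-size and center effects, two size groups, equal expected center sizes and no competing deaths.

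**What to change.** Make the primary comparison of 5-year DFS a weighted sum of within-stratum Kaplan-Meier differences, Σ wₛ(S_control,s − S_test,s), with wₛ the stratum's share of randomised patients, so that the result stays on the scale of the 5-point margin. Form the strata from tumor size and center, with small centers pooled. Stratify the supporting log-rank and regression analyses in the same way, and report the unstratified analysis as sensitivity.

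The cost is a few sentences in the protocol and analysis plan; no new data are needed. The one downside is that the pooling rule has to be fixed before outcomes are compared by arm. With about 11 events per full stratum, and fewer where competitive recruitment leaves a center small, unpooled strata can understate the standard error. Part of the apparent gain from full size-by-center strata may come from that. Combining over tumor size with a few pooled center groups is the safer choice.
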